#### Secondary analysis

Logistic regression analyses of appropriate subgroups (for example age or symptom profile) will be used to identify where an alternative cut-off may be more appropriate.

### Bias and confounding

There will be duplicate determination of the serum MMP-9 level and dual data entry. Information on potential confounders, for example injuries or chronic illnesses that may lead to a raised serum MMP-9, will be collected at the general practice clinic. National and published data will be used to identify selection bias based on socio-demographic or symptom status. The analysis will be adjusted to take account of any confounders or selection bias. The blood sample for serum MMP-9 determination will be taken on the same day as the colonoscopy to improve comparability. All blood samples will be analysed in the same laboratory to ensure standardisation of measurement and reporting. The technician doing the MMP-9 ELISA assay and the clinician undertaking the colonoscopy will be blinded to the patient's symptoms as reported on the questionnaire.

### Ethical approval

This study has been approved by South Birmingham Research Ethics Committee: reference 05/Q2707/133.

## Discussion

Colorectal cancer is a major cause of morbidity and mortality. Most colorectal cancers arise from adenomas and there is a period for early detection by screening, but available tests have risks, are unacceptable to many, have high false positive rates, or are expensive.

A pilot study of patients attending a specialist clinic has indicated that serum MMP-9 is an accurate and acceptable test for colorectal cancer. The sensitivity and specificity of a test can, however, vary in populations with different disease spectrums. This study will evaluate the accuracy of serum MMP-9 as a test for colorectal cancer in a primary care population, the target population for screening.

This study will establish the potential of serum MMP-9 as a screening test for colorectal cancer. If it is confirmed as accurate and acceptable, this serum marker has the potential to assist with reducing morbidity and mortality from colorectal cancer.

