### Pilot work

We have completed a pilot study of 300 patients (all "urgent" referrals) attending a specialist colorectal clinic. In this high prevalence group (27% with pathology), the accuracy of serum MMP-9 for colorectal neoplasia was 73% (sensitivity 99%, specificity 63%, positive predictive value 50%, negative predictive value 99%). Serum MMP-9, therefore, appears to have the potential to be a useful screening test for colorectal neoplasia. There is a strong possibility, however, that our pilot was affected by spectrum bias. Although the sensitivity and specificity of a test are unaffected by disease prevalence, the performance of a diagnostic test can vary according to the spectrum of the population being tested, that is the severity and clinical presentation of the disease [19,20]. Evaluation of the accuracy and acceptability of serum MMP-9 in a primary care population, the target population for a potential screening test, is required to inform the utility of serum MMP-9 screening in the general population.

*Feasibility work *for this study has also been undertaken. One hundred and ninety eight questionnaires were distributed in December 2003. There was a return rate of 74% (n = 146), and 59% (n = 116) returned a completed questionnaire. Twenty four respondents (21% of 116) had symptoms other than only abdominal bloating and/or anal symptoms, and 13 of these people (54% of 24) agreed to take part in the study. Eleven, of the 13 agreeing to take part, were invited to a general practice research clinic, eight returned the availability slip and seven agreed to attend. Six of these people attended a research clinic and all were eligible and consented to have a blood sample and colonoscopy.

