## Methods/Design

### Study design

Community based survey with embedded diagnostic test accuracy evaluation. Accuracy of MMP9 will be assessed by comparison with the gold standard, colonoscopy. A cohort aged 50–69 years with lower gastrointestinal symptoms will be identified using a questionnaire. People who are willing to participate will be given further information at a general practice based research clinic and informed consent will be obtained. Participants will have a blood sample for serum MMP-9 determination and a colonoscopy.

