### Selection of participants

Lists of eligible persons will be generated from practice registers. These lists will be scrutinised by GPs, who will remove all patients deemed inappropriate to receive a questionnaire (according to criteria defined above).

A postal questionnaire will assess symptoms over the past three months, the acceptability of screening tests for colorectal cancer, risk factors for colorectal cancer, and willingness to take part in the study. The symptoms are based on the Department of Health (DoH) referral guidelines for suspected colorectal cancer [23,24]. One reminder will be sent two weeks later. Respondents who describe any colorectal symptoms (except only abdominal bloating and/or anal symptoms) and express willingness to take part in the evaluation will be sent an information leaflet and an invitation to attend a research clinic at their general practice.

GPs will be notified by fax of people who report symptoms that meet the criteria for urgent referral under the two week standard [24]. Such people will continue to be eligible for the study, although the GP will be made aware of their symptoms before the person is invited to a general practice based research clinic. Regular reports of symptoms (except abdominal bloating and anal symptoms) reported by all respondents will be provided to GPs. Reports of all people meeting the criteria for urgent referral and who decide not to fully participate in the study will be regularly provided to their GP.

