### Justification of sample size

All types of colonic polyps have potential for malignant change but this is more common with increasing size, a villous growth pattern and more severe dysplasia [25]. Increasing age, adenoma size and a villous component have been associated with risk for high grade dysplasia [26].

In the USA, 11% (n = 329) of 3121 people aged 50–75 years without symptoms of lower gastrointestinal disease who had a complete colonoscopy had advanced colonic neoplasia (adenoma with a diameter of at least 10 mm, or villous features, high grade dysplasia, or invasive cancer) [27]. If large tubular adenomas were excluded, about 6% (n = 155) of people had lesions. About 32% (n = 105) of the 329 people only had lesions proximal to the rectum and sigmoid colon.

In Norway, 13% (n = 25) of 193 people aged 62–73 years who were offered a colonoscopy or flexible sigmoidoscopy and had a full colonoscopy had a high risk adenoma (adenoma greater than or equal to 10 mm and/or villous components and/or severe dysplasia) [28]. About 39% (n = 11) of the 28 high risk lesions were not in the rectum or sigmoid colon. In the UK, high risk lesions (greater than or equal to three adenomas, a polyp greater than 1 cm, tubulovillous or villous histology, severe dysplasia, malignancy, or greater than or equal to 20 hyperplastic polyps) were found in 5% (n = 1905) of 40674 people aged 55–64 years who were screened using flexible sigmoidoscopy [9]. This will not include proximal lesions that could be found on colonoscopy.

Any test that might usefully be employed to screen for malignant or premalignant colorectal lesions should have a high sensitivity to minimise the false negative rate. Based on our pilot data and conservatively assuming a community prevalence of 6% [9,27,28]. a sample of 700 people would be sufficient to estimate sensitivity within 3% (95% confidence) and specificity within 4% (95% confidence). If the community prevalence of high risk lesions is greater than 6%, our estimate of sensitivity will have greater precision.

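### MMP-9 accuracy is measured only in people with lower-GI symptoms, but the protocol presents them as the screening target population, so the accuracy conclusion needs narrowing

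*Protocol article*

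**What the plan says.** **Who is tested.** Study design: "A cohort aged 50–69 years with lower gastrointestinal symptoms will be identified using a questionnaire". Selection of participants sends the clinic invitation to "Respondents who describe any colorectal symptoms (except only abdominal bloating and/or anal symptoms) and express willingness to take part in the evaluation". People with no symptoms, or with only bloating and/or anal symptoms, are therefore not invited to the accuracy evaluation. The same section keeps people who meet the urgent-referral criteria in the study: "Such people will continue to be eligible for the study, although the GP will be made aware of their symptoms". The Methods/Design part of the abstract also states the symptom restriction.

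**What is concluded.** Pilot work justifies the study by saying that evaluation "in a primary care population, the target population for a potential screening test, is required" to inform use of the test for screening in the general population. The Discussion says that accuracy will be evaluated "in a primary care population, the target population for screening", and then: "This study will establish the potential of serum MMP-9 as a screening test for colorectal cancer". The abstract's Discussion says the same. The Aim and primary objective 1 do not mention symptoms.

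**The protocol's own view of spectrum.** Pilot work says that the pilot, made up entirely of urgent referrals to a specialist clinic, may well have been affected by spectrum bias, because performance can change with severity and clinical presentation. The Discussion repeats the principle.

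**Adjustment.** Bias and confounding says that external data will be used to identify selection bias, including by symptom status, and that the analysis will be adjusted for it.

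**The concern.** The accuracy sample is selected on symptoms, which means on clinical presentation. That is the feature the protocol says can change test performance. The screening conclusion, however, concerns a general population that mostly lacks those symptoms. Lesions in people without symptoms may be smaller or earlier, and non-diseased people without symptoms may have a different MMP-9 distribution. Sensitivity, specificity and the cut-off could therefore all differ.

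The interpretation of the primary result is at stake. As planned, the study can describe how MMP-9 performs in symptomatic people in primary care. Read as the Discussion invites, the same figures would be taken as evidence about people who were never tested.

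**Working it through.** **1. The plan's own figures reproduce, so N is not the problem.** Inputs from Justification of sample size: N = 700, prevalence 6%. Inputs from Pilot work: sensitivity 99%, specificity 63%.
- Diseased: 700 × 0.06 = 42. Non-diseased: 658.
- Sensitivity half-width: 1.96 × √(0.99 × 0.01 / 42) = 3.01 points (stated: 3).
- Specificity half-width: 1.96 × √(0.63 × 0.37 / 658) = 3.69 points (stated: 4).
- Pilot at 27% prevalence: PPV 49.7%, NPV 99.4%, accuracy 72.7%, which match the stated 50%, 99% and 73%.

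**2. How much of the age group the accuracy sample leaves out.** Pilot work (feasibility): 24 of 116 completed questionnaires had qualifying symptoms.
- Qualifying: 24/116 = 20.7%. Not qualifying: 92/116 = 79.3%.
- The 95% Wilson interval for the non-qualifying share is about 71–86%. It applies to responders only. The 92 include people with only bloating and/or anal symptoms as well as people with none.

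**3. Why adjustment cannot supply the missing information.** Let π be the share of lesions in the screening population that fall in the qualifying group. Then

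Se(screening) = π × Se(qualifying) + (1 − π) × Se(non-qualifying),

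and specificity has the same form. The study estimates Se(qualifying). It has no MMP-9/colonoscopy pair from the non-qualifying group, so the second term has no data, and π is not observed either. Weighting by symptom status can rebalance among tested people, but it cannot create a stratum with no observations. The subgroup analyses by symptom profile (Secondary analysis) also lie within the tested group.

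**4. Illustration only; these inputs are assumed, not in the documents.** Suppose lesion prevalence in the qualifying group is 1, 2, 3 or 5 times that in the rest. With r the ratio and s = 24/116, π = s·r / (s·r + 1 − s) = 21%, 34%, 44% or 57%. Keep 99% sensitivity in the qualifying group:

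| Assumed sensitivity in the rest | Sensitivity in the screening population |
|---|---|
| 90% | 92–95% |
| 80% | 84–91% |
| 60% | 68–82% |

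In every row the study itself would report about 99%.

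**5. Predictive values if accuracy did transfer.** PPV = p × 0.99 / [p × 0.99 + (1 − p) × 0.37].
- p = 5%: 0.0495 / (0.0495 + 0.3515) = 12.3%.
- p = 6%: 0.0594 / (0.0594 + 0.3478) = 14.6%.
- p = 11%: 0.1089 / (0.1089 + 0.3293) = 24.9%.

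These are projections. They assume the very transfer that is in doubt, so they do not measure the fault. They show only why predictive values need a stated population.

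**The case against.** The case for the plan has real strength. The Discussion speaks of potential and makes it conditional on the test proving accurate and acceptable. The abstract discloses the symptom restriction. Finding people by postal questionnaire from practice lists is a long step away from urgent clinic referrals. Primary objective 2, acceptability as a screening test, is assessed through the initial questionnaire, which is sent without regard to symptoms, so part of the screening question is answered in a broad sample. All of this stands. It limits the point but does not close the gap between the accuracy sample and the accuracy conclusion.

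Several stronger readings are tempting and are not supported:
- *The protocol claims it will establish MMP-9 as a population screening test.* It claims to establish the potential.
- *The pilot's spectrum problem is simply repeated.* It is the same kind of problem, probably smaller, although people meeting urgent-referral criteria remain eligible.
- *The pilot's 50% PPV is carried over to screening.* Pilot work labels it as coming from a high-prevalence group, and the summary that follows rests on sensitivity and negative predictive value.
- *The sample size is wrong because one prevalence source covers people* "without symptoms of lower gastrointestinal disease who had a complete colonoscopy had advanced colonic neoplasia". The 6% is described as conservative, and a higher prevalence helps sensitivity. At 11%, 700 × 0.89 = 623 are non-diseased and the specificity half-width is 1.96 × √(0.63 × 0.37 / 623) = 3.8 points, still within 4.
- *A projected PPV of 12–15% is no better than the 12% quoted for FOB.* The FOB figure is for cancer, whereas the 6% prevalence is for high-risk lesions. The endpoints differ, so the comparison should not be made.

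**Conclusion.** The point holds as a mismatch between the population in which accuracy is measured and the population to which the conclusion is addressed. Both are stated outright, so this is not a detail lost in condensing the protocol. Sensitivity, specificity, the ROC cut-off, PPV and NPV will describe symptomatic people aged 50–69 in primary care. By the protocol's own reasoning they cannot be assumed to apply to people without symptoms, and the planned adjustment cannot make them apply.

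The best indication of scale is that about 79% of feasibility responders (interval about 71–86%) fell outside the accuracy evaluation. This rests on 116 completed questionnaires out of 198 sent. The documents do not allow the size of any difference in accuracy to be estimated. A reader might infer that the screening statement must be deleted altogether. That goes too far, because the acceptability component supports part of it.

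**What to change.** - Restate the Aim, primary objective 1, the abstract and the Discussion so that accuracy refers to people aged 50–69 with lower-GI symptoms in primary care.
- In Pilot work and the Discussion, stop describing the accuracy sample as the population targeted by screening.
- Keep the sentence on screening potential but qualify it: accuracy in asymptomatic screening needs separate evaluation. The questionnaire acceptability objective can stay as it is.
- Report observed PPV and NPV for the symptomatic group. If values at screening prevalence are shown, label them as projections that assume sensitivity and specificity transfer (with pilot values, PPV 12.3%, 14.6% and 24.9% at 5%, 6% and 11%).

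The cost is some rewording, a label on any projected values, and a narrower claim. Recruitment and sample size do not change.
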